### Follow-up assessments

The following parameters will be assessed and recorded during the follow-up time of 7 days or until discharge, whichever is earlier:

**Maternal:**

**• Blood lost:** Blood lost from incision to 2 hours after the CS will be estimated. The amount of blood in sponges and drapes used in surgery and blood loss from suctioning (excluding amniotic fluid) will be estimated. At the end of surgery, a calibrated obstetric drape will be used for 2 hours. 

**• Reaction at site of IM injections**: Each IM injection site will be inspected for local reactions at the same time as PK blood sampling and then daily thereafter (for 7 days or until prior discharge).

**• Vital signs**: Participants will have their blood pressure, temperature, heart rate and respiratory rate recorded at the time of each PK blood sampling and daily until discharge or day 7.

**• Treatments:** Data on treatments likely to influence PK levels of TXA (blood product transfusion and IV fluids administration, TXA or other antifibrinolytics) will be collected from the time of TXA administration up to the time of the last PK sample.

**• Adverse events:** As described in section “Pharmacovigilance”, will be recorded up to 7 days.

**• Clinical diagnosis of PPH:** Clinical diagnosis of PPH up to 24 hours after birth (total blood loss of >1000 mL, or any blood loss sufficient to cause haemodynamic instability or requires further treatment).

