### Description of investigational product and justification of the dosage, route of administration, administration schedule and treatment duration

In this study, women will be randomised to four groups:

1.
**IV TXA GROUP:** 30 women will receive 1 g of TXA by IV route. IV TXA treatment rapidly achieves the plasma levels of TXA needed to inhibit fibrinolysis and prevent excessive bleeding. Pharmacological research has shown that an IV dose of 1 g TXA maintains therapeutic plasma levels for around 3 hours, the period when the risk of bleeding is greatest
^
12,
19
^. However, the TXA PK and PD in pregnant women has not been described so far.2.
**IM TXA GROUP:** 30 women will receive 1 g of TXA by IM route. Studies of IM TXA in healthy volunteers report good absorption and no adverse effects
^
11,
12
^. The dose will be given as two 5 mL (0.5 g each) injections into the thigh (rectus femoris or vastus lateralis) or buttocks (gluteal muscles) muscles, depending on a clinical assessment of muscle mass
^
12
^. The 1 g dose (10 mL) is divided to reduce the volume injected (5 mL is considered the upper limit)
^
20
^. The injections will be given using the most appropriate needle size for IM administration from the sites stock (1" between 19 - 25 gauge and from 1 ½ inches up to 3" for large adults) using the Z-track method to seal the medication in the muscle
^
20
^.3.
**TXA SOLUTION ORALLY:** 30 women will receive 4 g of TXA oral solution. The dose was selected because of the 50% oral bioavailability and because previous and preliminary PK data show that the absorption through the oral route is much slower than through the IV or IM routes, with much lower maximal concentration (Cmax)
^
12,
13,
19,
21
^. Therefore, higher doses are needed to reach therapeutic levels, according to simulations. The oral route (tablets or solutions) is well characterised
^
22–
24
^, but oral TXA PK and PD in pregnant women have not been described so far.4.
**NO TXA CONTROL:** 30 women will receive no TXA and will be the control group for PD, blood loss and safety data.

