### TXA administration and timing of biological samples

The time of the TXA administration is T
_0_. One blood sample will be taken for PK prior to drug administration.

Post TXA administration blood samples will be taken at different time points during 24 h as per the schedules in
Figure 3. We understand that the care of the participant takes priority over the sampling schema and that sample times will inevitably differ from those indicated. If it is not possible to obtain a sample at the scheduled time, the sample should be collected as soon as feasible with the exact time of collection recorded. Reasons for any delay will be recorded. Where there are less than six evaluable PK samples obtained after TXA administration from a participant, this participant will be replaced in the study.

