### Collection and storage of biological samples

Only one blood sample for PK analysis will be collected at baseline for women who are randomised to receiving no TXA. Samples for D-dimer, full blood count (FBC) and renal function will be collected.

Maternal blood will be taken from a cannula to avoid multiple venepuncture as follows:

Two samples of 3mL each will be taken for FBC and two samples of 3mL each for renal function. Blood samples will be collected in purple top EDTA tubes for FBC and yellow top tubes with separation gel and clot activator for renal function.

Five samples for D-dimer of 3 mL for each sample of blood to be taken in collection blue top tubes containing 3.2% sodium citrate. Blood samples for D-dimer, FBC, and renal function will be collected from the hospitals and analysed by a local central laboratory. The laboratory will be asked to store the sample used for D-dimer analysis until the end of trial to allow for repeat tests if needed. In the event of failure of any of the PK samples, this will be used as a back-up and will be destroyed at the end of the trial.

Each maternal PK sample require about 20 µL of blood taken using a Mitra
^®^ cartridge from a finger prick (2 × 10 µL samples taken on the 2 cartridges of the same device to have one primary and one confirmation sample if needed). Sites will be provided with written procedures on how to obtain the blood sample using the Mitra
^®^ cartridge. Cartridges will be labelled with the date and time the sample was taken and with the participant Study Identification number.

The total volume of blood taken (less than 35 mL) should have no clinical impact on the participant.

To obtain the umbilical PK blood sample, once the umbilical cord is clamped, it is wiped with antiseptic and a syringe and needle is inserted into the vein in the umbilical cord to withdraw a small amount of blood. PK samples from the umbilical cord and neonates will also be taken using the Mitra
^®^ cartridge system as described above.

A blood sample from the neonate (2×10 µL) will be taken using the Mitra
^®^ cartridge at the time of the routine clinical heel prick test to avoid additional heel pricks.

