### Trial restrictions and the use of concomitant medication

Participants should receive all clinically indicated treatments. There is no restriction on the use of concomitant medication. In the event non-trial TXA is given during the time of the PK blood sampling, the dose, route of administration, date and time should be recorded on the case report form (CRF).

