## Statistics and data analysis

### Sample size calculation

Using PFIM 3.2.1 software
^
51
^ and based on the population pharmacokinetic parameters determined in a meta-analysis of the different pharmacokinetic studies published in healthy volunteers and data through the IV route in trauma patients
^
13,
52
^, a sample size of 120 participants will allow estimates (relative standard errors < 30%) of the pharmacokinetic parameters of the intravenous, intramuscular and oral administration of TXA. Optimal maternal blood sampling times were evaluated and are as follows: immediately before TXA administration, and 15, 30 minutes, 1h, 2h, 4h, 8h, 12h and 24h after TXA administration. However, if in exceptional circumstances a sample cannot be taken at the optimal stated time, flexibility in blood sampling is allowed as detailed in the section “TXA administration and timing of biological samples”. The actual sampling time must be recorded.

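### As worded, the no-TXA arm has no post-baseline window for recording non-trial TXA, other antifibrinolytics, transfusion or IV fluids, and fewer vital-sign readings than the TXA arms

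*Protocol article*

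**What the plan says.** Under Follow-up assessments, the maternal Treatments item covers blood products, IV fluids, TXA and other antifibrinolytics. These data "will be collected from the time of TXA administration up to the time of the last PK sample".

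Trial restrictions and the use of concomitant medication places no limit on other drugs. It asks for the details of non-trial TXA under one condition: "In the event non-trial TXA is given during the time of the PK blood sampling".

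Collection and storage of biological samples says: "Only one blood sample for PK analysis will be collected at baseline for women who are randomised to receiving no TXA". TXA administration and timing of biological samples defines T0 as the time of TXA administration and names no equivalent for controls.

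The maternal Vital signs item has these measurements "recorded at the time of each PK blood sampling and daily until discharge or day 7". Baseline data collection also records a set for everyone. Sample size calculation gives the PK times as "immediately before TXA administration, and 15, 30 minutes, 1h, 2h, 4h, 8h, 12h and 24h after TXA administration".

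The description of the investigational product says that the 30 women without TXA "will be the control group for PD, blood loss and safety data". Description of trial population allows all standard interventions if PPH develops.

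**The concern.** The recording rules are anchored to two events, a TXA dose and a series of PK samples, that exist only in the three TXA arms. Applied to all four arms, they require treatment data from 90 women and, after baseline, none from the 30 who form the comparator.

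The D-dimer and blood-loss comparisons across groups (Pharmacodynamic analysis and Efficacy) need these data. A control given TXA for bleeding is no longer untreated, and transfusion or fluids may also affect the measurements. If such treatment is documented in three arms but not in the fourth, nobody can later describe how far the control arm departed from no TXA, or allow for it.

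Vital signs have a related problem. Safety parameters plans the number (%) of women with abnormal values in each randomised group. A woman measured more often has more chances of an abnormal value, whatever the drug does.

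**Working it through.** The plan's own total agrees with its arms: 4 × 30 = 120. The precision target (relative standard errors below 30%) cannot be re-run, because the article does not give the PK parameters behind it. This point does not depend on it.

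**Step 1. Treatment window, by arm.**

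| | TXA arms | No-TXA arm |
|---|---|---|
| Start event | TXA dose (T0) | none |
| End event | last PK sample, nominally 24 h | the single baseline sample |
| PK samples | 1 before + 8 after dosing = 9 | 1 at baseline, 0 after |
| Length after baseline | 24 − 0 = 24 h | 0 h |

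Read literally, the rule for non-trial TXA has the same limit: the period of PK sampling in a control is one moment before surgery.

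**Step 2. Vital-sign readings.** With d daily readings, the TXA arms have 9 + d and the controls 1 + d.

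| Daily readings (d) | TXA arms | No-TXA arm |
|---|---|---|
| 1 | 10 | 2 |
| 3 | 12 | 4 |
| 7 | 16 | 8 |

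The gap is always 8 readings. If the baseline set is taken separately from the first PK sample, it adds one to both columns and leaves the gap unchanged.

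To show the direction of the distortion, assume that each reading has a 5% chance of being abnormal, independently, with no drug effect. The chance of at least one abnormal reading is 1 − 0.95^n:

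- d = 1: 1 − 0.95^10 = 40% against 1 − 0.95^2 = 10%
- d = 3: 1 − 0.95^12 = 46% against 1 − 0.95^4 = 19%
- d = 7: 1 − 0.95^16 = 56% against 1 − 0.95^8 = 34%

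The 5% and the independence are assumptions. Readings on one woman minutes or hours apart are likely to be correlated, which narrows these gaps.

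**Step 3. How many controls could be affected.** The article gives no rate of non-trial TXA use, so a range is assumed. With rate c among 30 controls, the expected number is 30c and the chance of at least one is 1 − (1 − c)^30.

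| Assumed c | Expected women | Chance of at least one |
|---|---|---|
| 5% | 1.5 | 0.79 |
| 10% | 3 | 0.96 |
| 20% | 6 | 0.999 |
| 30% | 9 | > 0.999 |

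Over this range at least one such woman is likely, but the number could be small.

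**The case against.** The case against has several parts.

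- **Purpose of the window.** The Treatments item concerns treatments that may alter TXA levels, and controls are outside the PK analysis. For that purpose the window is adequate. It does not serve the D-dimer, blood-loss and safety comparisons, and no other item in the article collects these treatments in controls.
- **General follow-up.** Follow-up assessments opens with recording for 7 days or until discharge. The Treatments item then sets its own narrower window, which the general line does not override.
- **A looser reading.** The period of PK sampling could be taken as the 24 hours common to the trial, and controls have a nominal reference about 1 hour before caesarean section. This is a fair reading, but staff should not have to infer it.
- **Unseen material.** Figures 2 and 3, the CRF and the full protocol may already define control times. This limits confidence. A reader might infer that the control D-dimer samples have no clock; the article does not support that, because it refers those times to Figure 3.

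A reader might also infer that rescue TXA in controls would go unseen. That is too strong. Clinical diagnosis of PPH is recorded in every arm and includes loss needing further treatment, so many of the women concerned could be identified, although without drug, dose or time. Nor are vital signs nearly absent in controls: baseline and daily readings remain.

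Finally, a reader might attribute any dilution of the treatment contrast to this wording. If a treated control behaves like a woman in a TXA arm, a fraction 1 − c of the contrast remains (90% at c = 10%, 80% at 20%), whether or not her TXA is recorded. Recording only allows the dilution to be examined. TXA given in response to bleeding also cannot change blood already lost.

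**Conclusion.** The point holds as a defect of wording that makes data capture unequal by arm. For treatments, the stated rule gives 24 hours of recording in each TXA arm and no post-baseline window in the no-TXA arm. This follows from the article's own sentences and needs no assumed figure. For vital signs, controls have 8 fewer readings; the between-arm percentages are not comparable if every reading counts, and the article does not say which readings do.

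The consequence cannot be sized from the document. The contamination range and the 5% abnormality rate are illustrations. The conclusion also assumes that the figures, CRF and full protocol do not already set a control window. The change should be made, because treatments not captured at the time may not be reliably recoverable later.

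**What to change.** 1. Define a reference time zero for the no-TXA arm, for example randomisation or the scheduled dosing time about 1 hour before caesarean section.
2. Reword the Treatments item and the non-trial TXA rule so that TXA, other antifibrinolytics, transfusion and IV fluids are recorded from time zero to 24 hours in all four arms.
3. Take vital signs at the same nominal times in every arm. Alternatively, restrict the between-arm comparison of abnormal values to time points common to all arms.
4. If Figure 3 or the CRF already gives control times, align the text with them.

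The cost is protocol and CRF wording, routine treatment data for 30 women and, under the first option in item 3, a few extra vital-sign readings in those women. No extra blood is needed. How the analysis then uses recorded non-trial TXA is a matter for the statistical analysis plan.

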**Neonate:**

**• Apgar score** recorded 1 and 5 minutes after birth. This is a standard clinical test given to all newborns. This test checks a baby's heart rate, muscle tone, and other signs to see if extra medical care or emergency care is needed.

**• Adverse events:** As described in section “Pharmacovigilance”, will be recorded up to 7 days.

### End of trial for participants

The trial ends at discharge, death or at 7 days, whichever occurs first.

### Distinction between standard care and research

The only departure from standard care is the TXA given about 1 hour prior to CS and extra blood sampling. Additionally, we will regularly inspect the IM injection sites.

### Blood sample analysis

**
*TXA quantitation.*
** TXA will be measured with liquid chromatography coupled to mass spectrometry according to an analytical method validated following the European Medical Agency (EMA) guideline on bioanalytical method validation (EMEA/CHMP/EWP/192217/2009Rev.1 Corr.2)
^
50
^. The method is linear in the range 0.1–1000.0 µg/mL, accuracy is between 85.9 and 110.8% and precision <8.2%.

**
*D-dimer quantitation.*
** Blood for D-dimer assays will be assayed at a central laboratory. A citrate-containing tube will be properly filled and mixed via inversion. It will be transported to the laboratory and analysed within 3 hours. Quantification will be done by immunoassay.

### Premature exit of trial participant

Participants may exit the study at any time and for any reason. A previously given consent can be withdrawn. The investigator can withdraw a participant from the trial for any safety reason or if it is in the participant's best interest.

If a participant exits the trial prematurely or withdraws consent or refuses consent for continuation, data collected up to time of premature exit will be used. Participants who withdraw from the trial with less than six post treatment PK samples will be replaced to ensure the four intervention groups remain balanced.

**
*Monitoring participants after the premature termination of treatment.*
** In case of an adverse event to the participant or her baby, the investigator will complete an adverse event report and monitor the event until the end of her participation in the research or until it has resolved or reached a stable state.

**
*Procedure for replacing participants.*
** If consent procedures are complete but the TXA dose is not given in full, the participant will be replaced.

When oral TXA is given and the participant vomits within the first hour of receiving the intervention, this participant will be replaced in the study. However, data collection for the participant will continue to the trial end.

Where the CS is delayed and takes place more than 2 hours after the administration of the intervention, the participant will be replaced in the study. However, data collection for the participant will continue to the trial end.

If a participant receives the TXA dose but there are less than six post treatment evaluable PK samples obtained after TXA administration, this participant will be replaced in the study. However, data collection for the participant will continue to the trial end.

Data collected from the replaced participants will be used.

## Trial treatment

### Description and regulatory status of investigational medicinal product(s)

TXA is sold globally under a variety of trade names for the treatment of bleeding due to general or local fibrinolysis in adults and children from one year of age
^
30
^. Several brands are licenced for use globally.

Participants will receive a licenced marketed form of TXA which will be purchased in each country.

### Known drug reactions and interaction with other therapies

TXA solution for injection should not be added to blood for transfusion, or to injections containing penicillin.

### Trial restrictions and the use of concomitant medication

Participants should receive all clinically indicated treatments. There is no restriction on the use of concomitant medication. In the event non-trial TXA is given during the time of the PK blood sampling, the dose, route of administration, date and time should be recorded on the case report form (CRF).

### Assessment of compliance with treatment

IV, IM or oral TXA will be given by investigators at the participating site who will record the date and time of administration and who administered the investigational medicinal product (IMP). For the IM route, the body location of each TXA injection will also be recorded. If the IMP is not fully administered, the reason for this will be recorded in the CRF. The following will not be considered non-compliance with the protocol: where a participant dies before receipt of the IMP or where a clinical or protocol allowed reason is given for non-administration of the IMP.

## Pharmacovigilance

Maternal events which occur as a consequence of the CS, or events which commonly occur in this population independent of exposure to the TXA administration, and those which are study endpoints do not need to be reported as an adverse event. Congenital or genetic abnormalities in neonates do not need to be reported as adverse events as these events are collected routinely. All other events fulfilling the criteria below should be reported. If a participant (both maternal and neonate) develops an adverse event, they should be treated in line with local procedures. In the definition below, participant refers to both maternal and neonate (s).

The flow chart of the safety reporting is shown in Additional file 6 (see
*Extended data*)
^
49
^.

More details on pharmacovigilance are available in Additional file 3 (see
*Extended data*)
^
49
^.

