### Secondary endpoints

•Blood concentrations of D-dimer over time•TXA concentration in umbilical cord and neonate after birth•Local reactions at IM injection sites•Adverse events (maternal and neonate)•Neonate status Apgar score•Measured blood loss from start of CS to 2 hours after•Clinical diagnosis of PPH

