### Randomisation

After collecting baseline data, enrolled participants will be randomised into one of the four groups described in “Description of investigational product and justification of the dosage, route of administration, administration schedule and treatment duration”. The sequence for each dosing cohort will be created using computer-generated random numbers, using blocking to ensure the required balance in the allocation of participants to treatment arms. The allocation ratio will be 1:1:1:1. 

An IT coding expert supported by a statistician who are not involved in the conduct of the trial will prepare the randomisation codes. Eligibility will be confirmed and randomisation done via an online database. Once the code is generated, the trial intervention will be prepared and administered by a trained trial team member. Participants and all trial staff will be blind to treatment allocation until randomisation is completed.

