### Safety parameters

**Full blood count and renal function parameters:** Descriptive statistics for baseline and follow-up will be presented for each laboratory parameter. Changes from baseline as well as shift tables for laboratory parameters will be presented. All laboratory values will be classified as normal, below normal (low), or above normal (high) based on normal ranges supplied by the central laboratory. Frequencies of abnormal values will be presented in tabular form. For purposes of analyses, laboratory results based upon standardized units will be used.

**Vital signs:** Descriptive statistics for blood pressure, heart, and respiratory rate will be presented in tabular form with mean, median, standard deviation and range (minimum and maximum) as appropriate. Number (%) of women with abnormal values in each randomised group will be presented.

**Expected adverse events (collected routinely as outcomes for all participant):** For each event, the number (%) of women in each randomised group will be presented.

**Other adverse events:** Adverse events will be coded by primary system organ class and preferred term using the Medical Dictionary for Regulatory Activities (MedDRA). The number of events (n) and number (%) of participants with events will be presented. Events will be presented separately for maternal and neonates.

**IM injection skin reaction:** Number (%) of women with a reaction and severity of reaction will be presented.

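### Residual maternal adverse events can be left unreported on a causal judgement made with allocation known, so the 'Other adverse events' counts by arm are open to differential under-reporting

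*Protocol article*

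**What the plan says.** The Pharmacovigilance section sets three exemptions. The first covers "Maternal events which occur as a consequence of the CS". The second covers "events which commonly occur in this population independent of exposure to the TXA administration". The third says that "those which are study endpoints do not need to be reported as an adverse event". The default for the remainder is "All other events fulfilling the criteria below should be reported". The exemption is worded as one from adverse event reporting as such, not only from expedited reporting.

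The trial is open label. Under Randomisation, "Participants and all trial staff will be blind to treatment allocation until randomisation is completed"; after that, allocation is known.

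Safety of the three routes is a secondary objective, and adverse events are a secondary endpoint. The 30 women given no TXA "will be the control group for PD, blood loss and safety data".

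The section on the safety of TXA says that all women are routinely assessed for nausea, vomiting, diarrhoea, thrombotic events, seizures and injection site reactions. Safety parameters tabulates these expected events by randomised group, separately from 'Other adverse events', for which "The number of events (n) and number (%) of participants with events will be presented".

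**The concern.** The first two exemptions turn on cause. Someone at the bedside has to decide whether an event came from the operation, or would be common without TXA. That person knows whether TXA was given.

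For a common event in a no-TXA woman, independence from TXA is settled in advance. For the same event in a TXA woman it is a judgement. Staff acting in good faith can therefore apply different thresholds by arm, and the resulting counts feed the 'Other adverse events' table. Adverse events are also part of what the data monitoring committee reviews.

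Two things are at stake. Reported frequencies may differ between arms when true frequencies do not. And if TXA raises the frequency of an event classed as common or surgical, the increase may never be recorded.

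**Working it through.** The article gives no event rate, power or effect size for safety; the sample size rests on the precision of the PK parameters. There is thus no stated figure to reproduce beyond 4 × 30 = 120. The check is a comparison of passages followed by an illustration.

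**Which events are exposed**

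| Source in the article | Events | Attribution filter? |
|---|---|---|
| Routine assessment of all women | nausea, vomiting, diarrhoea, thrombotic events, seizures, injection site reactions | No |
| Safety parameters | blood count, renal function, vital signs | No |
| Pharmacovigilance, feeding 'Other adverse events' | all remaining maternal events | Yes |

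The section on the safety of TXA also cites a systematic review of 25 studies that found more minor transient events with TXA. It names nausea, vomiting, headache and dizziness. The first two are on the routine list. Headache and dizziness are not, so they fall in the last row. If staff class them as common or as due to the operation, they need not be reported.

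**What differential exemption does to the counts**

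Inputs: 90 TXA women and 30 controls (1:1:1:1 allocation, 30 per arm). Assumptions: a true risk p equal in all arms, and a fraction e of events exempted.

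Reported risk = p × (1 − e)

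Reported risk ratio = (1 − e_TXA) / (1 − e_control)

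With p = 0.20 the true counts are 90 × 0.20 = 18 and 30 × 0.20 = 6.

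| e_TXA | e_control | Reported, TXA (90) | Reported, control (30) | Risk difference | Risk ratio |
|---|---|---|---|---|---|
| 0.5 | 0.5 | 9.0 | 3.0 | 0 | 0.5/0.5 = 1.0 |
| 0.3 | 0.5 | 12.6 | 3.0 | +4 points | 0.7/0.5 = 1.4 |
| 0.2 | 0.6 | 14.4 | 2.4 | +8 points | 0.8/0.4 = 2.0 |
| 0.6 | 0.2 | 7.2 | 4.8 | −8 points | 0.4/0.8 = 0.5 |

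The ratio does not depend on p. In the third row, each TXA arm of 30 would show 30 × 0.20 × 0.8 = 4.8 events against 2.4 in controls. At this size, two or three unreported women change how the table reads.

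**What equal exemption does**

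The first row leaves the ratio intact but loses half the events. If a class of event is exempt altogether (e = 1 in every arm), the reported counts are 0 and 0, whatever TXA does to that event. With e = 0 in every arm, the ratio under no true effect is 1.0.

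**The case against.** The best defence is that the second exemption describes a class of background events, common with or without TXA, and that a class is the same in every arm. On that reading the ratio is not distorted. This stands in part. It does not help with events attributed to the operation, which can need a case-by-case decision. Nor does it help with a class that goes unrecorded: an effect of TXA on headache, for example, would then be lost in all arms equally.

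A second defence is that the article is condensed and refers to the full protocol (Additional file 3) and a safety flow chart, which may list the exempt events or have them recorded elsewhere. That cannot be checked, and the absence of a list is not held against the article. The point rests on the rule that the article does state.

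A third is that the table is descriptive, with no stated test against no TXA. True; this limits the consequence. A table by arm beside a named safety control will still be read as a comparison.

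Some stronger readings are tempting and are not supported:

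- **The whole safety comparison is biased.** The routine events, laboratory values and vital signs are collected without an attribution filter.
- **Nearly everything in the control arm is exempt.** The rule covers only common or surgery-related events; an uncommon event with another cause stays reportable.
- **The endpoint exemption is circular because adverse events are an endpoint.** Safety parameters separates routinely collected outcomes from other adverse events, so the sensible reading is that it avoids double reporting.
- **Neonatal events are affected in the same way.** The surgical and common-event exemptions are worded for maternal events, and neonates are routinely assessed.

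**Conclusion.** The point holds for maternal events outside the routinely collected list. Their reporting depends on causal attribution by staff who know the arm, so the 'Other adverse events' counts are open to differential under-reporting, and a true TXA effect on a common event can be missed. Headache and dizziness are concrete examples from the article itself.

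The documents do not show that differential attribution occurs, nor fix its direction. The range of 0.5 to 2.0 rests wholly on the assumed exemption fractions and is not an estimate of bias in this trial. A reader might infer from the 2.0 that a false excess on TXA is to be expected; reversing the fractions gives 0.5, and equal fractions give 1.0. The primary PK endpoint is untouched. The change should be made because safety by route is a stated objective and the remedy is cheap.

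**What to change.** Record every maternal adverse event on the CRF in all four arms to day 7 or discharge, whatever its presumed cause. Enter causality in a separate field, and tabulate by randomised group regardless of it. Keep the surgical and common-event exemptions for expedited reporting only.

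If full recording is thought too heavy, list the exempt common events in advance and capture each as an outcome in every arm, as is already done for nausea and vomiting. Headache and dizziness belong on that list.

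If the full protocol already does either, it is enough to bring the article's wording into line.

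The cost is protocol and CRF wording, plus more adverse event entries for about 120 women over at most 7 days. Recruitment had begun when the article was written, so a change of rule would need an amendment, and women enrolled earlier would have been recorded under the existing rule. Fuller recording does not remove open-label influence on subjective complaints; it removes only the attribution filter.
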